### Health economic evaluation:

A detailed economics analysis plan will be approved by the PSC prior to analysis of follow up data. The analysis plan will be informed by published literature supplemented with descriptive analysis of pooled (unblinded) baseline data to identify key covariates for imputation and regression models for the follow up data. The methods used to deal with missing follow-up data will be determined according to the extent and pattern of missing data (e.g. multiple imputation, missing indicator or propensity score methods) [28, 90, 91].

The economic data will be analysed using an intent-to-treat approach. The cost perspective is that of the care providers/funders (health and social care and prison services) and the time horizon for the primary care analysis is the 6-month follow up of the trial. The primary measure of interest for the economic analysis is the incremental cost effectiveness ratio (ICER), a joint measure of costs and outcomes. Accordingly, no statistical tests of differences in mean costs or outcomes will be conducted. The ICER is estimated using the formula shown in Fig. 4.

**Fig. 4 Fig4:**
[figure not shown]
Formula for incremental cost effectiveness ratio (ICER)

Regression analysis will estimate the net costs and health benefit of the PROSPECT programme, controlling for baseline covariates and used to generate cost-effectiveness acceptability curves (CEAC) for the primary and all sensitivity analyses. Covariates will be determined in the same manner as for the statistical analysis and used to generate cost-effectiveness acceptability curves (CEAC) for the primary and all sensitivity analyses.

The estimates of incremental costs and outcomes from the regression will be bootstrapped to simulate 10,000 pairs of net cost and net outcomes of the intervention group for a cost effectiveness acceptability analysis, as recommended by for health technology appraisals [65]. This will include generating the cost-effectiveness plane, net benefit statistic, cost effectiveness acceptability curves and probability the PROSPECT programme is cost effective compared to usual care [65].

In the absence of a universally agreed threshold willingness to pay value per QALY gained we plan to use a mid-estimate willingness to pay threshold value of £15,000 per QALY gained, with a range of £0 to £30,000 threshold values. The final mid-estimate and range of threshold values will be determined on the basis of published guidance at the time of analysis [12].

Sensitivity analysis will be used to test the impact of assumptions and data on the ICER and results of the cost effectiveness acceptability analysis. These will include: the method of handling missing data, the health benefit measure used in the ICER and the time horizon of the analysis. The choice of sub-groups will be informed by discussion with the clinical team about prison or prisoner characteristics (moderators) likely to affect either costs or health benefit.

There is limited evidence about the effectiveness and cost-effectiveness of suicide prevention programmes in prison settings. Hence, we will use a decision analytic model to extrapolate over a longer time horizon than the 6-month trial-based analysis. The development and analysis of the model will include:A focused review of published evidence and guidelines to identify evidence about:The effectiveness of suicide prevention programmes in prison settings and the maintenance of any effect beyond 6-months.Existing economic models and methods used to evaluate suicide prevention programmes in prison settings.Data about the costs, outcomes and cost-effectiveness of suicide prevention programmes in prison settings.The model structure will be developed iteratively with the full team of researchers and clinical experts. The starting point will be a draft model structure developed from the focussed review and materials developed as part of the research programme.The model will be populated using data from the 6-month trial plus clinical and economic data from the focussed review that allow extrapolation over a longer time period. All the model analyses will use a cost effectiveness acceptability approach to estimate the likelihood that the PROSPECT programme is cost effective.The model will use the 6-month trial data and data from the focussed review to extrapolate the costs, outcomes and cost-effectiveness estimates over longer time frames. We will use assumptions/scenarios about the longer-term impact of the intervention, which will be developed with the full research team. We will use threshold analysis to determine the minimum effect required for the PROSPECT programme to be cost-effective. If there is no observational or trial-based evidence from the review about the likely effectiveness of suicide prevention programmes beyond 6 months, the model will be used to conduct extensive threshold and scenario analyses to assess how effective the PROSPECT programme would need to have more than a 50% likelihood of being cost-effective.

### Process evaluation

Alongside the RCT, there will also be a process evaluation that investigates the nature and context in which the intervention is delivered. Specifically, we will ask “What are the facilitators and barriers to the future implementation of the PROSPECT programme across the prison estate?” The design of the process evaluation follows the MRC guidance on process evaluations of complex interventions. We will draw on a recognised implementation framework, iPARIHS (Integrated Promoting Action on Research Implementation in Health Services, [38], to inform data collection and analysis. The mixed method process evaluation will draw on multiple sources of data to create a rich picture of implementation in practice, enabling us to understand both barriers and facilitators to delivery of the intervention, and to determine if and how implementation success or failure contributes to the RCT outcomes.

Data to inform the different elements of the process evaluation will be collected via semi-structured interviews with staff and prisoner participants, an observational study, and quantitatively with regard to the level of implementation of the Prospect programme. The strategy has been developed to enable the process evaluation research questions to be addressed, but sufficiently flexible to enable the process evaluation to adapt to the needs of the project. A key consideration for the data collection strategy was to ensure a balance was struck between capturing a representative breadth of data and views as well as the depth of information to understand participant journeys through the Prospect programme.

### Semi-structured interviews:

Semi-structured interviews will be conducted with participants receiving the Prospect Programme, practitioners delivering the Prospect Programme, the PROSPECT researchers recruiting participants, and staff employed in key roles within the four host prisons. For prisoner participants, we will interview some participants only once, but others will be interviewed up to three times to understand the barriers and facilitators of participation at key time points in delivery of the Prospect programme. Across the four prisons, we plan to recruit up to 48 prisoner participants who are receiving the Prospect programme. Of these, we anticipate interviewing between six and 24 participants up to three times, depending on the needs of the project. There will be some prioritisation to interview participants during the internal pilot stage to identify any early implementation issues. We will also interview between 8 and 16 staff participants, selected from prison-based staff involved in key roles in the care and management of prisoners who present a risk to themselves. Furthermore, the trial therapists / practitioners directly involved in delivering the Prospect programme (n = 4–10), and those with experience working as a PROSPECT trial researcher (n = 4–10) will also be invited to take part in semi-structured interviews. In order to capture early implementation challenges faced by the practitioners, as well as obtaining a good understanding of how such challenges are resolved or persist throughout the life of the trial, we plan to interview each Prospect Practitioner and Researcher approximately every six months, up to a maximum of four interviews over the two years of the trial.

### Observational study

The purpose of the observations is to learn more about any contextual factors that could act as barriers or facilitators to the implementation of the PROSPECT intervention. In line with the I-PARIHs context construct, relevant contextual factors could include the priorities, culture, and relationships present within the establishments where PROSPECT is being delivered. We will use maximum variation sampling based on the observed characteristics of the professional sample. Across the four prison sites, we will recruit four to eight members of prison staff. Participants for this study will be identified from within the interview sample. The observations will be focused and targeted in nature and aim to explore any tensions/gaps/inconsistencies that emerge from the interview data, as well as relevant contextual factors. The observations will focus on planned activities attended by prison staff or Prospect staff who have taken part in semi-structured interviews. Observed activities MUST relate to the management of suicide or self-harm in prison. These could include (but are not limited to) ACCT reviews, safety intervention meetings, complex case meetings, and mental health case reviews or handover meetings. There can also be an element of snowballing. For example, if during the observations or semi-structured interviews other planned activities that would be beneficial to observe come to light, then these can also be pursued.

### Process evaluation analysis plan

We will produce descriptive statistics for the quantitative outcomes. For the qualitative data, we will combine interview transcripts and field notes recorded from the observation case studies in Nvivo. We will use Reflexive Thematic Analysis, guided by the iPARIHS framework, to create higher order themes. The initial qualitative analysis will be completed blind to the trial outcome to enable open exploration of the themes. We will use a convergence coding matrix to synthesise the different data sources [87]. The synthesis will be interpretative rather than aggregative (as the qualitative and quantitative data cannot be formally combined). We will tabulate the data from each part of the evaluation according to the MRC implementation constructs. This will be in the form of summary statistics for the quantitative data and higher order themes and selectively coded exemplar text from the qualitative data. We will organise data corresponding to each site, to enable us to check for differences and similarities across settings. The analysis team will iteratively review within and across the organised data to identify patterns, guided by the iPARIHS framework (i.e. attending to interacting roles of context, facilitation, recipients and innovation) and reflecting back on the pre-existing prototype logic model [15]. The goal output is to produce a revised “Type 4” logic model [56], whereby the prototype logic model is tested and adapted using the process evaluation data. This enables completion of a contextually sensitive and evidence based final logic model for future delivery of the programme.

### Fidelity measures

In the feasibility trial, a protocol was developed for offering the PROSPECT programme for suicidal prisoners which incorporated checks for patient accessibility/acceptability, practitioner adherence, and therapeutic alliance [74]. Despite prisoners being described as a difficult-to-engage clinical group, over 70% of participants randomised to therapy attended five or more sessions, out of a maximum of 20, with an average of 9 sessions attended. The ‘Did Not Attend’ rate was less than 6%. Ratings of practitioner adherence to the protocol and participant acceptability were above acceptable levels [74].

Within the nested process evaluation, we will assess treatment integrity by monitoring adherence/fidelity to the PROSPECT programme protocol and practitioner competence. Treatment fidelity will be ensured through regular supervision of the trial practitioners and assessed by audio recordings of therapy sessions, where permission to do so has been granted by the participant, with 10% (randomly chosen) rated for adherence to the treatment manual by a member of the project team using the bespoke Treatment Module Checklist, which lists the permitted treatment modules. Also, practitioners and participants will be invited to complete an assessment of the therapeutic alliance [39], after approximately four sessions and again at the end of the therapy.

### Custodians of the data

It should be noted that the Chief Investigator is the custodian of the data.

## Discussion

### Strategies to improve and monitor treatment adherence

The PROSPECT programme will be delivered by accredited Psychological Practitioners (e.g. BABCP accredited Psychological Practitioners or HCPC registered Clinical/Forensic/Counselling Psychologists) with one practitioner allocated to each of the four prisons in the intervention arm of the trial. Trial Therapists / practitioners will already be well trained in delivering psychological therapies, but they will also undergo an intensive training period to gain familiarity with the specifics of the PROSPECT programme, led by the programme team members. The training will involve a combination of interactive lectures and seminars, modelling, role-plays, reading assignments, and homework exercises, which will be delivered by the Chief Investigator (DP) who has extensive training and several years of experience with the CBSP intervention. We anticipate this training will be delivered once at the outset of the trial, although individual training will also be delivered for any replacement practitioners who join the trial at a later date. During the trial, practitioners will receive fortnightly supervision from the Chief Investigator (DP) and other experienced Clinical Psychologists familiar with the treatment protocol. Teleconferencing technologies will be used to ensure practitioners working in both the Northwest and Yorkshire regions can access clinical supervision. Supervision will focus on individual client work, techniques delivered by the therapist, intervention planning and problem-solving any barriers to implementation. Adherence will be monitored throughout the intervention delivery period using a structured therapy delivery diary.

### Ethics, governance and safety

#### Strategies for assessment and management of risk

The safety of participants will be of paramount importance throughout the trial. Whilst some participants may feel some distress whilst completing some of the patient questionnaires, there is no reason to believe that research procedures will increase suicide risk to participants. An established literature has now refuted the idea that discussing suicidal behaviour *automatically* increases the risk of such behaviour [7, 18, 19, 46] with findings suggesting that individuals are more likely to derive benefit from participation than experience harm [85]. Nevertheless, a pertinent ethical issue of this study may be the increased burden for participants in completing the self-report assessments.

From the outset, we will take care to inform participants exactly what is involved in taking part, and allow for as many comfort breaks as needed, with all assessment measures handled sensitively and at the participant’s preferred pace for completion. In a previous study, we found that many participants reported positive experiences of taking part in suicide prevention research, in terms of feeling involved in important research, the cathartic value of talking about suicide, and an enjoyable inter-personal experience [85].

This trial may actually benefit individual participants since cognitive behavioural therapies are not routinely available for suicidal patients in prison. Furthermore, all participants taking part in this trial, in both the PROSPECT therapy programme plus TAU and the TAU alone groups, will receive an enhanced level of monitoring such that any participant deemed to be at suicidal risk will be identified and immediately directed to appropriate care available within the host institution. Our feasibility trial with this patient group reported a modest benefit of entering the TAU condition, likely due to the additional monitoring and sensitive manner of the research assessors [74]. No treatments will be withheld during the trial, with all participants having access to the support they were receiving before the research study (e.g. Prison GP, Mental Health Team, Drug & Alcohol Team), so there is no expected disadvantage in taking part. Participants will not receive payment for participating in the trial, but assurances will be sought from the host prison governor that participants will be authorised to miss their usual work responsibilities in order to attend therapy or research appointments without affecting their usual wage.

### Participant risk management

Inherent in the nature of the population eligible for the trial is the risk of suicide. All participants will remain under the care of the prison GP throughout the duration of the trial. The prison GP will be responsible for all patient-level treatment and management decisions, including prescribing, referral and assessment of risk. This arrangement will be made clear to all clinicians and prison staff involved in the ongoing care of patients in this trial. The pragmatic nature of this trial means that we will not seek to influence this arrangement.

In addition to the usual arrangements described above, participants in the trial will also be subject to our detailed policies and standard operating procedures, informed by good clinical practice, for monitoring and managing suicide risk during all researcher encounters with trial participants. The distress protocol will be followed should any participant disclose suicidal thoughts during any encounter with the research team, or if the research team have reason to suspect the participant is experiencing an increase in suicide risk. Research Assistants (RA) will be well-trained in our distress protocol and receive regular clinical supervision to ensure adherence to the procedure. Participants’ suicide risk status is assessed at each of the trial’s assessment interviews, including follow-ups, with specific questions focussed upon suicidal thoughts and plans. The distress protocol worked effectively in our feasibility trial where no serious adverse reactions were recorded.

### Researcher risk management

All members of the research team, which includes practitioners and RAs, will abide by the lone working policies of their employer(s). For the aspects of the research that take place in a prison setting, the research team will undertake the necessary induction training and security clearances as determined by the individual prison and will abide by the health and safety policies and procedures of the prison. A risk assessment for the study has been conducted and a researcher safety protocol is in place that all research staff will be familiar with prior to undertaking research activities. All researchers will receive clinical supervision on a fortnightly basis and will be able to speak to the CI or Programme/Trial Manager between clinical supervision sessions.

There is a possibility that research participants may tell the researcher information that the researcher will have a duty to disclose to the appropriate authorities. Participants will be informed via the Participant Information Sheets that the researchers may have to disclose any information that raises concerns about participant safety or the safety of others, information regarding undisclosed illegal acts or any current plans of future illegal activities behaviour that is against the prison rules, or information that raises concerns about terrorist, radicalisation or security issues. Additionally, prison staff or other professionals taking part in the research will be informed that researchers will have a duty to inform the appropriate authorities should they disclose information about misconduct or poor practice.

### COVID-19 risk

COVID-19 is likely to be an ongoing, dynamic risk factor throughout the duration of the trial. This includes risk to the research staff, practitioners, and participants in terms of increased risk of getting COVID-10, but may also interfere with recruitment of participants, data collection, and delivery of the PROSPECT programme. Individual prisons have, in collaboration with Her Majesty’s Prison and Probation Service (HMPPS), developed protocols for safe working. These protocols include varying levels of restrictions depending upon the number of cases of COVID-19 within each prison and the level of cases/transmission within the wider geographical area of each prison.

At all times, the research team will adhere to the protocols in place at each of the prisons to minimise risk to the participants, members of the research team, and to the staff working in the prison. This will include the wearing of protective clothing, using meeting rooms with adequate space to allow for social distancing, and potentially limiting contact with participants to remote contact. In the event of the latter of these restrictions, the research team will continue to deliver the PROSPECT programme via phone or tablet as discontinuing the therapy may present a risk to participants who have already started therapy. Research activities, including recruitment and data collection, will continue where possible, although may be paused for a period of time until face-to-face contact is permitted again. This may have implications for the timely completion of the RCT, but as the study is being run in four prisons any restrictions in one prison can be offset by increasing research activity in the other prisons.

### Safety reporting

#### Adverse Events (AEs)

An adverse event (AE) reporting system will be used on the trial. Suicidal ideation, self-harm, harm to others and property will be routinely recorded and it is expected that these will occur for some participants. These will include, ideation alone with no behaviour (suicidal ideation or self-harm ideation), self-harm or suicidal behaviour (cutting self, biting and breaking the skin, severely scratching or running anything on the skin, using corrosive substances on the skin, sticking sharp objects into the skin, pulling out hair, burning with a cigarette lighter or match, scolding the skin, swallowing objects, choking or blocking airways, inserting objects into body cavities, overdosing with prescribed medication, overdosing with non-prescribed medication, taking illicit substances (not including medication), taking poisonous substances, inducing vomiting, over-eating, eating something that is known to cause an allergic reaction, food or fluid refusal, refusing medication, violence towards an inanimate object (e.g. a wall or door), ligaturing/hanging, drowning, severing body parts, electrocuting), events involving others (threats to harm others / violence, actual harm to others / violence). It should be noted that these may be Serious Adverse Events (SAEs) depending on the severity of injuries and outcomes of the behaviour. These events do not require further follow up unless there is evidence that these are research related but each event should be recorded from consent until 1 month after the final follow-up assessment is completed. Any untoward medical occurrence that is not included in the definition above will not be reported.

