Improving access to psychological treatments is a UK government priority with some psychological approaches particularly effective in the reduction of suicide behaviour. In their meta-analysis, Tarrier, Taylor and Gooding [84] found psychological therapy directly targeting suicide behaviour, relative to usual treatment, had an overall positive effect on suicidal behaviours (combined Hedge’s g = –0.59, *p* < 0.001, 95%CI: –0.81 to –0.37). However, this evidence was restricted to community patients and there are substantial differences between community and prison environments. Social climates in prison are characterised by a necessary focus upon security (rather than care), with restrictive treatments delivered by under-resourced healthcare teams amidst a prisoner culture where help-seeking is seen as vulnerability to be exploited (Pratt et al., 2016). Prisoners have limited access to psychological therapies targeting suicidal behaviour often due to organisational or professional boundaries. Prison and healthcare staff may not believe that they have the necessary skills to deal with the needs of suicidal prisoners and therefore may not be willing to offer treatment. Ex-offenders have expressed a strong desire for more ‘taking therapies’ for vulnerable prisoners, with a preference for a pragmatic, solution oriented approach to the use of emotional regulation techniques and overcoming suicidal thoughts and behaviours – views much aligned with the academic literature [48, 68, 71, 75].

Psychological therapies can be criticised for describing a range of principles and techniques, only some of which are optimal in reducing suicidal behaviour. We have addressed this issue by developing a theoretically based psychological model of suicide behaviour that specifies the precise mechanisms to target within a suicide prevention psychotherapy [34, 47, 73]. Informed by this theoretical and empirical work, we have developed and manualised an individualised talking therapy intervention, Cognitive Behavioural Suicide Prevention (CBSP), which aims to address and amend the key aspects described by our psychological model. The feasibility of delivering CBSP therapy has already been piloted in the community with people experiencing psychosis [83], and mental health inpatients [36].

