### Demographic, clinical and criminological data

In addition to the outcome measures detailed above, a range of demographic (age, gender, ethnicity), clinical (mental health diagnoses, previous suicide behaviour) and criminological (index offence, sentence length, previous imprisonments) details will also be collected at baseline. The researcher will also complete a contact sheet for each participant, which will include contact numbers and addresses provided by the participant, as well as a list of services they are likely to be in contact with post-release. This sheet will be completed in collaboration with the participant and the participant will sign the form to confirm they give the research team permission to contact them via the relevant services. Furthermore, clinical and prison records will be accessed, subject to participant consent, to collect relevant information that the participant is unable to self-report accurately, e.g. psychiatric diagnoses, offence details, serious incidents of self-injury and violence.

See Fig. 3 for further information on which time point each procedure or measure is completed.

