#### Serious Adverse Events (SAEs)

All SAEs occurring from the time of consent until 1 month after the final follow-up assessment completion will be recorded on the SAE report form and emailed to the Prospect Trial Manager and CI (as sponsor’s representative) immediately and within 24 h of the research staff becoming aware of the event. Any change of condition or other follow-up information will be reported to the Trial Manager and CI as soon as it is available, or at least within 24 h of the information becoming available. Events will be followed up until the event has resolved or a final outcome has been reached.

The Trial Manager and CI will review the SAE form. If the SAE is related to participation in the trial, the CI will review the expectedness in relation to the nature or severity of which is not consistent with the effects or consequences of participation in a psychological intervention trial. All adverse events that are research related will be reported by the CI to the relevant host prison responsible clinical team and the Data Monitoring and Ethics Committee (DMEC) on a regular basis and in an expedited fashion. Fatal or life-threatening events will be reported to the Programme Steering Committee, the DMEC and the relevant Ethics Committee within seven days of knowledge of such cases.

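### The closed adverse-event list has no category for threats, bullying, coercion or violence done to the participant by others, so non-serious victimisation cannot be compared between arms

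*Protocol article*

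**What the plan says.** In the Protocol article, Safety reporting, the Adverse Events section opens with its scope: "Suicidal ideation, self-harm, harm to others and property will be routinely recorded". A long list of specific behaviours follows. The only item about other people is "events involving others (threats to harm others / violence, actual harm to others / violence". On seriousness the section says: "It should be noted that these may be Serious Adverse Events (SAEs) depending on the severity of injuries and outcomes of the behaviour". It ends with an exclusion: "Any untoward medical occurrence that is not included in the definition above will not be reported".

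The Serious Adverse Events section then states: "All SAEs occurring from the time of consent until 1 month after the final follow-up assessment completion will be recorded". It adds that research-related adverse events go to the prison's clinical team and the data monitoring committee. The article gives no separate definition of an SAE.

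Elsewhere, the Background places prison treatment "amidst a prisoner culture where help-seeking is seen as vulnerability to be exploited". It also says that prisoners hide emotion to avoid being victimised by other prisoners. The section on referrals and retention names victimisation among the real-world conditions that could affect recruitment and follow-up.

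**The concern.** An adverse-event list in a trial of a talking therapy should cover harms that the setting makes plausible, in both directions. This list goes down to over-eating and hair-pulling, yet being threatened, bullied, coerced or assaulted by another prisoner does not appear. Because the list is expressly closed, this is a stated restriction on what is recorded. It is not a detail left to a fuller document.

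The stake is the safety comparison. The trial is meant to inform wider implementation across the prison estate, and the ethics section says that no disadvantage from taking part is expected. For non-serious victimisation the trial as written could neither support nor contradict that statement. Self-harm that followed victimisation would be counted, but without its cause.

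**Working it through.** No arithmetic applies. The check is whether any route in the article would record harm done to a participant by others, in both arms.

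1. **Direction of the list.** The opening sentence covers ideation, self-harm, and harm to others and property. In "events involving others (threats to harm others / violence, actual harm to others / violence" the bare word violence could be read to include violence received. Two things point the other way: the opening sentence speaks of harm to others, and the seriousness sentence refers to the outcomes of the behaviour, which is naturally the participant's own. The plain reading is outward only.

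2. **Effect of the closing sentence.** A minor injury from an assault is an untoward medical occurrence outside the list, so it is not reported. Bullying, threats or coercion may not be medical occurrences, so the exclusion may not strictly reach them. They still fit no listed category, and nothing directs anyone to record them.

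3. **The SAE route.** "All SAEs occurring from the time of consent until 1 month after the final follow-up assessment completion will be recorded" sets no limit by event type, so a serious assault on a participant could be recorded. But "It should be noted that these may be Serious Adverse Events (SAEs) depending on the severity of injuries and outcomes of the behaviour" discusses seriousness only for the listed events, and the article does not define an SAE separately. Whether a serious assault counts is therefore unclear from these two sections.

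4. **The research-related route.** Research-related adverse events are passed on, but the preceding section has already fixed what counts as an adverse event.

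5. **Monitoring.** The between-arm trigger under Monitoring of adverse events names suicide-related events only.

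6. **Disclosure.** Under Researcher risk management, concerns about participant safety may be passed to the authorities. That is a duty to disclose, not event recording.

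7. **Records.** The section on demographic, clinical and criminological data allows extraction of "serious incidents of self-injury and violence". No direction is stated, so serious violence against a participant may be found there. Non-serious events are outside its wording, and it is not linked to adverse-event reporting.

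8. **Exposure by arm.** The therapy arm is offered up to 20 one-to-one sessions over 6 months; control participants have research appointments only. The work-release arrangement, "participants will be authorised to miss their usual work responsibilities in order to attend therapy or research appointments", covers research appointments too and so applies in both arms. The therapy arm has more contacts, but control participants are not without visible contact.

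None of these routes gives a by-arm count of non-serious harm received. For serious harm there are possible routes (3 and 7), neither of them explicit.

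**The case against.** A reader might infer that the protocol itself foresees victimisation as a harm of the therapy and then fails to record it. The documents do not support that. The Background presents exploitation of help-seekers as a difference between prison and community, and emotional suppression as a challenge to engagement. The retention section treats victimisation as a threat to recruitment and follow-up. No passage calls it an expected effect of treatment, so there is no internal contradiction.

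A reader might also infer that this harm differs between arms by design. That goes too far. Every participant, controls included, is on the ACCT system or was within four weeks before consent, so all are already identified as at risk. Usual care can include referral to the Mental Health Team. The pilot offered the therapy as a programme, a word prisoners already used for ordinary activities.

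Nor is it right that such harm would go wholly unrecorded. Serious assaults may enter as SAEs or through the records. Suicidal behaviour that follows victimisation is itself a co-primary outcome and a listed event. Interviews with up to 48 therapy recipients may bring victimisation to light, although without a control group. The full protocol, which is not shown, may define an SAE, so the uncertainty about serious assaults is a point to clarify and not an error.

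These objections narrow the point considerably. They leave the gap itself in place: non-serious harm received from others has no category, under a list that says it is closed.

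**Conclusion.** The point holds in this limited form. The closed list omits threats, bullying, coercion and violence directed at the participant, so non-serious victimisation cannot be compared between arms. The article also leaves unclear whether serious assaults on a participant count as SAEs. That therapy attendance might raise the risk rests on inference from the Background and the session schedule, and should be presented as such.

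No magnitude can be attached. The documents give no victimisation rate in either arm, so any statement about power would rest on invented figures. The conclusion assumes that the list printed in the article is the one in use and that its interpersonal item is read outward, as its opening sentence suggests. The change is worth making because it is cheap and widens what the trial can say about safety; it does not affect the primary analyses.

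**What to change.** Add one category to the Adverse Events list: threats, bullying, coercion or violence towards the participant by others. Record it the same way in both arms, using one fixed question at the existing 6-month interview and the prison records already accessed with consent, with extraction extended to this category. State explicitly whether a serious assault on a participant is an SAE. Report the category by arm to the IDMC, as a descriptive comparison with no power claim.

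The cost is one more question at an interview that already takes place, in a population where respondent burden matters, and a little more record extraction. No new visit or staff is needed, and nothing in the delivery of the therapy changes.
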